#### Pathology

The esophageal resection and lymphadenectomy specimens will be processed and analyzed according to national and international guidelines by the department of pathology. In addition to the separately sent lymph node stations, the esophageal surgical resection specimen will be carefully analyzed for retained lymph nodes and structures macroscopically suspicious for lymph nodes will be embedded. All lymph nodes under 5 mm will be totally embedded for microscopic evaluation, larger lymph nodes will be totally embedded in slices of 3–4 mm thick. Microscopically, a circumscript area of lymphoid cells containing a follicular architecture and/or a subcapsular sinus is identified as a lymph node. In the final report the exact localization and number of lymph nodes found will be reported.

Initial microscopic evaluation will be performed by standard H&E staining. In case of suspicion of micro-metastasis (0.2–2.0 mm) or isolated tumor cells in the lymph node, or in case of suspicion of residual tumor cells in patients with extensive response to neoadjuvant therapy, additional keratin stains will be performed. A metastatic lymph node is defined as a lymph node with tumor cells. Lymph nodes containing micro-metastasis or isolated tumor cells are also considered as metastatic lymph nodes but will be also recorded separately. Lymph nodes with regression after chemoradiation with isolated tumor cells will be considered as metastatic lymph nodes, however, these also will be recorded separately, so that the prognostic value of these isolated tumor cells can be determined. The same applies to fibrotic lymph nodes without vital tumor cells. These are so called preneoadjuvant therapy N+ nodes. In case of an adenocarcinoma of the esophagus, Her2-status will be analyzed (immunohistochemistry and SISH).

#### Follow-up

Patients will be followed up until 5 years after the operation. Follow-up will usually be scheduled (but differences between countries exist) every 3 months the first year, every 6 months the second until the fourth year and once yearly until the fifth year. Investigations are performed according to national guidelines.

### Statistical analysis

#### Primary study parameter(s)

Numbers and percentages of resected lymph nodes and lymph node metastases will be given per lymph node station (Fig. 1). Tumor location and invasion depth will be categorized. Patients with adenocarcinoma and squamous cell carcinoma and patients with and without neoadjuvant therapy will be analyzed separately.

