## Background

Survival rates following an esophageal resection for esophageal carcinoma vary from a median of 25 to 74 months [1, 2]. An important parameter for survival is lymph node status [3–12]. The distribution of lymph node metastases depends on tumor characteristics such as tumor location, histology, invasion depth, and on neoadjuvant treatment [13–20]. However, the precise distribution pattern is unknown.

In the Netherlands, among other countries, curative treatment for patients with esophageal carcinoma consists of neoadjuvant chemoradiation followed by surgery [21, 22]. The radiation field during neoadjuvant treatment and the lymphadenectomy during surgery depend on the location of lymph node metastases but no consensus has been reached on the extent of the lymphadenectomy [23]. If a distribution pattern of lymph node metastases of esophageal carcinoma can be identified, the optimal neoadjuvant and surgical treatment can be determined.

The administration of neoadjuvant therapy itself can also influence the distribution of lymph node metastases [13]. Neoadjuvant chemoradiation may be able to sterilize metastatic lymph nodes. Lymph nodes inside the radiation field are affected by both radiotherapy and concurrent chemotherapy, whereas lymph nodes outside the radiation field are affected by chemotherapy only. Nevertheless, recent studies show that also after neoadjuvant therapy, the extend of lymphadenectomy is directly related to survival [24]. Therefore, not only the metastatic behavior of untreated esophageal carcinoma is an important factor, also the pattern after neoadjuvant therapy can provide valuable information for the optimal extend of lymphadenectomy after chemo (radio)therapy.

Especially for adenocarcinoma the distribution of lymph node metastases has not yet been described in large series that report on a complete 2- or 3-field lymphadenectomy [13, 14]. Also, different classification systems for lymph node stations are used in current literature, leading to incomparable studies. Besides the limited and heterogeneous evidence, also the significant morbidity involved in esophageal surgery makes the treatment choices demanding considering that the removal of more lymph nodes may lead to a more invasive procedure, possibly increasing the risk for postoperative morbidity.

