#### Neoadjuvant therapy

In case of potentially curative disease (cT1-4a, N0–3, M0) patients may be treated with neoadjuvant therapy, this however, may differ per country and usually consists of chemotherapy or chemoradiotherapy.

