#### Radiation fields

One coronal, 1 sagittal and 3 axial CT-images of the radiation field is documented in the medical file, to assess lymph nodes stations incorporated in the radiation field. An anatomical description of the radiation field will be given according to highest and lowest radiated lymph node station. An in-field lymph node is defined as a lymph node within the clinical target volume. Clinical target volume fields as defined gross tumor volume plus a margin for sub-clinical disease spread.

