#### Secondary study parameter(s)

The sensitivity, specificity, and positive and negative predictive values of EUS and PET-CT will be reported. Perioperative morbidity and mortality will be summarized descriptively. For each patient group (squamous cell versus adenocarcinoma, with and without neoadjuvant therapy), explorative cluster analyses will be performed to identify subgroups of patients with different patterns of lymph nodes metastases. Potentially relevant characteristics at the time of surgery like age, gender, tumor location, tumor invasion depth, tumor differentiation, vaso-invasive growth will be included in the analysis. No restrictions will be applied to the number of clusters in each analysis, but the ratio of the largest cluster size to the smallest cluster size should preferably not exceed the value of 3 and/or the smallest cluster size should be minimally 30 patients. Characteristics introducing patient outliers will be excluded and one should further be able to attribute meaning to the resulting cluster profiles. Clusters that show the phenomenon of skip metastases will be noted. The resulting clusters will be evaluated for the diffusion pattern of future metastases during follow-up (descriptive analysis), the number of future metastases during follow-up (Poisson regression or generalized estimation equation, whichever appropriate), for 3- and 5-year overall and disease-free survival (Kaplan-Meier survival analysis). Multivariate analysis will be performed using the Cox hazard regression method. The univariate analysis, including all baseline parameters, will serve as the basis for the multivariate Cox hazard regression model. Variables showing association (*p* < 0.10) with survival in univariate analysis will be included in the multivariate analysis. Age and sex will be included in all multivariate analyses. Results are presented as hazard ratio with exact 95% confidence interval (95% CI). After 5-years of follow-up the efficacy index will be determined (incidence of metastases to an area (%) × 5-year overall survival rate (%)). A log-rank test, Mann-Whitney U test, or χ^2^-test will be used as indicated to compare groups. A value of *p* < 0.05 will be considered statistically significant.

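### The neoadjuvant strata are only yes or no, so chemotherapy-only and chemoradiotherapy patients share one stratum although the protocol means to study both

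*Protocol article*

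**What the plan says.** All references are to the protocol article.

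- **Primary study parameter(s):** resected and metastatic nodes are counted and given as percentages per station. The two histologies are analysed separately, and "patients with and without neoadjuvant therapy will be analyzed separately".
- **Secondary study parameter(s):** the same groups carry over: "For each patient group (squamous cell versus adenocarcinoma, with and without neoadjuvant therapy), explorative cluster analyses will be performed".
- **Sample size:** the predefined strata that are meant to justify 5000 patients also distinguish neoadjuvant therapy only as present or absent.
- **Neoadjuvant therapy:** on the treatment given, "this however, may differ per country and usually consists of chemotherapy or chemoradiotherapy".
- **Background:** nodes inside a radiation field are exposed to radiotherapy and concurrent chemotherapy, whereas "lymph nodes outside the radiation field are affected by chemotherapy only".
- **Discussion:** the study is to examine whether chemoradiotherapy and chemotherapy affect both the presence and the location of nodal metastases. The optimal radiation field is named as one intended use of the results.

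**The concern.** The primary endpoint is a distribution over stations, reported in relation to neoadjuvant therapy. By the Background's own reasoning, chemoradiotherapy can change that distribution unevenly, because only some stations lie in the field. Chemotherapy alone has no such spatial boundary. Two treatments that are expected to alter the map differently are therefore placed in one stratum of the primary table.

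The choice between them follows national practice, and the study runs in 18 countries. The treated column then depends on which countries recruit most. A reader who wants the nodal map after chemoradiotherapy, or after chemotherapy, gets neither. The clusters formed within the treated groups inherit the same mixture.

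**Working it through.** **No figure to reproduce.** The target of 5000 is justified as enough for description and clustering. It has no precision target, power or effect size attached. The check is therefore a comparison of sections, an illustration of the mixing, and the cost of splitting.

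**1. Sections side by side.** Three sections (Sample size, Primary study parameter(s), Secondary study parameter(s)) use two levels of neoadjuvant therapy. Three others (Background, Neoadjuvant therapy, Discussion) distinguish chemotherapy from chemoradiotherapy. No section shown gives the three-level grouping that the Discussion's aim needs.

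**2. What the mixture does.** The documents give no station rates and no treatment mix, so all rates and shares here are assumed. Let *s* be the share of treated patients who had chemoradiotherapy.

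Pooled rate = *s* × p(chemoradiotherapy) + (1 − *s*) × p(chemotherapy)

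Take an in-field station with 30% involvement untreated, of which chemoradiotherapy clears 50% and chemotherapy 15%:

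- chemoradiotherapy: 0.30 × 0.50 = 15%
- chemotherapy: 0.30 × 0.85 = 25.5%
- *s* = 0.6: 0.6 × 0.15 + 0.4 × 0.255 = 19.2%
- *s* = 0.3: 0.3 × 0.15 + 0.7 × 0.255 = 22.35%, or about 22.4%

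Other assumed pairs of rates give the following range:

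| Chemoradiotherapy / chemotherapy rate | *s* = 0.2 | *s* = 0.5 | *s* = 0.8 |
|---|---|---|---|
| 5% / 20% | 17% | 12.5% | 8% |
| 10% / 20% | 18% | 15% | 12% |
| 15% / 20% | 19% | 17.5% | 16% |

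The pooled figure moves with the mix in every row. The movement is large when the treatments differ much and slight when they do not.

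**3. What splitting costs.** Half-width of the 95% confidence interval = 1.96 × √(p(1 − p)/n).

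- Now: 2 histologies × 2 levels = 4 groups, mean size 5000/4 = 1250.
- Split: 2 × 3 = 6 groups, mean size 5000/6 ≈ 833.

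With equal groups assumed:

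| Station rate | n = 1250 | n = 833 |
|---|---|---|
| 5% | 1.21 points | 1.48 points |
| 10% | 1.66 points | 2.04 points |
| 20% | 2.22 points | 2.72 points |

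Only the treated stratum is actually divided. If a treated stratum of 1250 were halved, then at a 10% rate 1.96 × √(0.09/625) = 2.35 points. If one treatment made up only 20% of it, the smaller part would have 1.96 × √(0.09/250) = 3.72 points. Both are still usable for description.

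**The case against.** The best defence has three parts.

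- **The text never says the two treatments will be pooled without further subdivision.** A journal article condenses the full protocol, and the analysis plan is not shown. This is fair as far as it goes: pooling is inferred from the only strata named. But the split is not left open. It is stated in three places, one of which calls the strata predefined.
- **A yes/no comparison answers a question that the Background really asks,** namely whether the same surgical strategy is justified with and without neoadjuvant therapy. That stands. However, three groups can be collapsed to answer it, whereas a two-group table cannot be taken apart to answer the Discussion's question.
- **The size is hypothetical.** That also stands. The main illustration moves by about 3 points between its two mixes, and less if the treatments act alike.

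A reader might go further and infer that the effect of radiation on location cannot be seen at all, because the field is described only by its highest and lowest station. The documents do not support this. Besides the description ("An anatomical description of the radiation field will be given according to highest and lowest radiated lymph node station"), the section on radiation fields requires images: "One coronal, 1 sagittal and 3 axial CT-images of the radiation field is documented in the medical file, to assess lymph nodes stations incorporated". It also sets the criterion: "An in-field lymph node is defined as a lymph node within the clinical target volume". The secondary endpoints include the ratio of nodal metastases inside and outside the field, and in-field or out-field nodal recurrence after chemoradiation. Nor do the documents give baseline rates from which to say in which direction any misclassification of stations would push the results.

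**Conclusion.** The point holds as a mismatch between the strata and the stated aim. As written, the treated percentages in the primary tables, and the treated groups for clustering, combine two treatments that the protocol itself expects to act differently by location. In the main illustration the pooled figure is 19.2% or 22.4%, where the separate figures are 15% and 25.5%. This rests on assumed rates and mixes. The true size depends on how far the treatments differ at each station and on who is enrolled.

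The consequence is limited to these tables and groups. The planned in-field and out-field endpoints remain, and the data are not lost if the treatment type is recorded for each patient. It is a cheap improvement to the primary analysis and does not invalidate the study.

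**What to change.** In the sample size section, the primary analysis and the cluster analyses, replace the yes/no split by three groups: no neoadjuvant therapy, chemotherapy only, and chemoradiotherapy. Present the per-station tables and form the cluster groups by these three levels within each histology. A combined treated column may be kept beside them for the with/without question.

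Confirm that the treatment type is recorded for every patient. The chemoradiation-specific recurrence endpoint implies that it is.

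The cost is one more column, two more cluster groups and somewhat wider intervals, as shown above. The three columns stay descriptive: because treatment follows country, differences between them should not be read as treatment effects without further adjustment.

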#### Secondary study parameter(s)

The sensitivity, specificity, and positive and negative predictive values of EUS and PET-CT will be reported. Perioperative morbidity and mortality will be summarized descriptively. For each patient group (squamous cell versus adenocarcinoma, with and without neoadjuvant therapy), explorative cluster analyses will be performed to identify subgroups of patients with different patterns of lymph nodes metastases. Potentially relevant characteristics at the time of surgery like age, gender, tumor location, tumor invasion depth, tumor differentiation, vaso-invasive growth will be included in the analysis. No restrictions will be applied to the number of clusters in each analysis, but the ratio of the largest cluster size to the smallest cluster size should preferably not exceed the value of 3 and/or the smallest cluster size should be minimally 30 patients. Characteristics introducing patient outliers will be excluded and one should further be able to attribute meaning to the resulting cluster profiles. Clusters that show the phenomenon of skip metastases will be noted. The resulting clusters will be evaluated for the diffusion pattern of future metastases during follow-up (descriptive analysis), the number of future metastases during follow-up (Poisson regression or generalized estimation equation, whichever appropriate), for 3- and 5-year overall and disease-free survival (Kaplan-Meier survival analysis). Multivariate analysis will be performed using the Cox hazard regression method. The univariate analysis, including all baseline parameters, will serve as the basis for the multivariate Cox hazard regression model. Variables showing association (*p* < 0.10) with survival in univariate analysis will be included in the multivariate analysis. Age and sex will be included in all multivariate analyses. Results are presented as hazard ratio with exact 95% confidence interval (95% CI). After 5-years of follow-up the efficacy index will be determined (incidence of metastases to an area (%) × 5-year overall survival rate (%)). A log-rank test, Mann-Whitney U test, or χ^2^-test will be used as indicated to compare groups. A value of *p* < 0.05 will be considered statistically significant.

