### Treatment of subjects

#### Staging

Preoperative staging will be performed according to national guidelines. This therefore, may differ per country. Usually, patients are staged with an endoscopy with biopsies, an endoscopic ultrasound, a PET-CT-scan of neck, thorax and abdomen and an ultrasound of the neck. An EBUS-TBNA will be performed if indicated. All patients are discussed in a multidisciplinary team (MDT).

A suspected lymph node is defined as a node larger than > 9 mm short axis or a node 5–9 mm short axis that is round, inhomogeneous and has an irregular border (2 out of 3). In case of PET-CT-scan, pathological nodes are those with FDG uptake, a short axis > 10 mm or those with a short axis between 5 and 9 mm that present with sharp borders.

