#### Restaging

After completion of neoadjuvant therapy patients will generally be restaged with a (PET-)CT scan to exclude distant metastases before patients are scheduled for surgery. In addition, the locoregional lymph nodes will be evaluated. The (PET-)CT will usually be performed 2–4 weeks after completion of neoadjuvant therapy.

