#### Surgery

If no metastases are detected, patients will be operated 5–12 weeks after completion of neoadjuvant therapy. This may differ per country and may depend on the type of neoadjuvant therapy. If no neoadjuvant therapy is administered patients are directly scheduled for surgery.

An esophageal resection with a 2- or 3-field lymphadenectomy can be performed via a thoracolaparoscopy, a thoracolaparotomy or a hybrid procedure and a cervical incision as indicated. A gastric tube or colonic interposition can be used for reconstruction. Lymph node stations may be dissected ex vivo (after enbloc resection with the specimen), in vivo, or partially ex and in vivo, and will be separately sent for pathological examination. Lymph node stations in close proximity to the tumor are preferably marked with sutures or beads to prevent damage to the specimen and circumferential resection margin.

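### Accuracy of EUS and PET-CT is not tied to scan time point or neoadjuvant status, so in treated patients staging scans may be scored against nodes that therapy has cleared

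*Protocol article*

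**What the plan says.** The accuracy analysis is one sentence under Secondary study parameter(s): "The sensitivity, specificity, and positive and negative predictive values of EUS and PET-CT will be reported". It names no reference standard, scan time point or treatment stratum. The matching item under Secondary endpoints speaks of preoperative diagnostics (EUS and PET-CT) and of what EBUS adds to staging with them.

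The sequence of events comes from other sections:

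- **Staging:** "Usually, patients are staged with an endoscopy with biopsies, an endoscopic ultrasound, a PET-CT-scan of neck, thorax and abdomen and an ultrasound of the neck". Neoadjuvant therapy may follow.
- **Restaging:** "After completion of neoadjuvant therapy patients will generally be restaged with a (PET-)CT scan to exclude distant metastases before patients are scheduled for surgery", and "In addition, the locoregional lymph nodes will be evaluated". EUS is not named here, and the brackets mean that the scan may be CT without PET.
- **Surgery:** "patients will be operated 5–12 weeks after completion of neoadjuvant therapy". For the others, "If no neoadjuvant therapy is administered patients are directly scheduled for surgery".
- **Pathology:** a node is metastatic if it contains tumor cells. Fibrotic nodes without vital tumor cells are treated as nodes that were positive before therapy.
- **Background:** "Neoadjuvant chemoradiation may be able to sterilize metastatic lymph nodes". The Discussion returns to this as a question the study will examine.

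Separate analysis by neoadjuvant therapy is written for the primary parameter and for the cluster analyses. It is not written for the accuracy sentence.

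**The concern.** The accuracy of a scan is judged against the state of the nodes when the scan was made. In a patient operated directly, the specimen gives that state. In a patient given neoadjuvant therapy, the specimen shows the nodes after treatment. A node that staging correctly called positive and that therapy then cleared is scored as a false positive. A positive node that staging missed and that therapy then cleared is scored as a true negative.

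The resulting error is systematic. A cohort of 5000 would make the wrong value more precise, not less wrong. Published figures for staging EUS and PET-CT in treated patients would mix test error with treatment response. Splitting by treatment alone protects the untreated estimate but does not repair the treated one. EUS is the more exposed of the two tests, because no post-treatment EUS is described.

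**Working it through.** The article gives no accuracy figure, nodal prevalence, clearance rate or treated share, so there is no planned figure to reproduce. The direction of the bias follows from algebra. The size can only be illustrated.

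**Set-up.** Let p be the true pretreatment nodal prevalence, Se and Sp the true sensitivity and specificity, and q the share of node-positive cases cleared by therapy. Assume first that q is independent of the test result and that no cleared node is recovered as fibrotic. Then, against viable tumor cells:

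- TP = p·Se·(1−q)
- FN = p·(1−Se)·(1−q)
- FP = (1−p)·(1−Sp) + p·Se·q
- TN = (1−p)·Sp + p·(1−Se)·q

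**Direction.**

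- Apparent PPV = true PPV × (1−q), so it always falls.
- 1 − apparent NPV = (1 − true NPV) × (1−q), so NPV always rises.
- Apparent specificity = [(1−p)·Sp + p·q·(1−Se)] / [(1−p) + p·q]. This is a weighted mean of Sp and 1−Se, so it falls for any test with Se + Sp > 1.
- Sensitivity = TP/(TP+FN) = Se, unchanged, but only because q does not depend on the test result.

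**Illustration, treated patients.** Assumed: p = 0.60, Se = 0.60, Sp = 0.85.

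- q = 0: TP 0.360, FP 0.060, FN 0.240, TN 0.340. Specificity 0.340/0.400 = 85.0%; PPV 0.360/0.420 = 85.7%; NPV 0.340/0.580 = 58.6%.
- q = 0.3: TP 0.252, FP 0.168, FN 0.168, TN 0.412. Specificity 0.412/0.580 = 71.0%; PPV 0.252/0.420 = 60.0%; NPV 0.412/0.580 = 71.0%.
- q = 0.5: TP 0.180, FP 0.240, FN 0.120, TN 0.460. Specificity 0.460/0.700 = 65.7%; PPV 0.180/0.420 = 42.9%; NPV 0.460/0.580 = 79.3%.

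**Varying the assumptions.** The first three columns of results show true → apparent, or apparent only where marked.

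| Scenario (all inputs assumed) | Specificity % | PPV % | NPV % | Sensitivity % |
|---|---|---|---|---|
| p 0.40, Se 0.60, Sp 0.85, q 0.4 | 85.0 → 75.5 | 72.7 → 43.6 | 76.1 → 85.7 | 60.0, unchanged |
| p 0.60, Se 0.80, Sp 0.70, q 0.4 | 70.0 → 51.2 | 80.0 → 48.0 | 70.0 → 82.0 | 80.0, unchanged |
| Base case, q 0.4, 70% treated, pooled with untreated (apparent) | 71.7 | 61.7 | 70.2 | 60.0 |
| Base case, q 0.4, 80% of cleared nodes recovered as fibrotic (apparent) | 80.2 | 78.9 | 61.9 | 60.0 |
| Base case, 50% of test-positive and 30% of test-negative cleared (apparent) | 63.2 | 42.9 | 71.0 | 51.7 |
| Base case, 30% of test-positive and 50% of test-negative cleared (apparent) | 73.2 | 60.0 | 79.3 | 67.7 |

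The last two rows show that sensitivity moves in either direction once clearance depends on the test result. The fourth row shows that counting fibrotic nodes as previously positive removes most of the error. Full recovery (effective q = 0) returns the true values, as does restriction to patients operated directly.

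**The case against.** The strongest reply is that the article does not commit itself to the faulty comparison. No sentence names viable-cell pathology after treatment as the reference standard. A condensed article may leave reference and strata to the full protocol or analysis plan. Three provisions already point towards a sound analysis: fibrotic nodes are identified as formerly positive, (PET-)CT is generally repeated after therapy with the locoregional nodes assessed, and treated and untreated patients are separated elsewhere. The wording about the fibrotic nodes could even mean that they count as metastatic, in which case most of the bias goes.

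Much of this stands and limits the point. The reference standard is an inference, although resection pathology is the only nodal reference described for every operated patient, since EBUS-TBNA is done only if indicated. What does not stand is the idea that nothing needs settling. The article spells out the treatment split for two other analyses and leaves the accuracy sentence unqualified. It does not link the fibrotic nodes to that analysis. It also leaves unclear whether such nodes are counted as metastatic or merely recorded.

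A reader might infer that the protocol asserts that therapy sterilizes nodes, or that the whole endpoint measures treatment effect instead of test accuracy. The text supports neither. It says only that chemoradiation may have this effect and gives no rate. Patients operated directly and restaging scans are outside the mechanism.

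**Conclusion.** The concern holds for one comparison: staging EUS or PET-CT in patients given neoadjuvant therapy, scored against viable tumor cells in the later specimen. There, specificity and PPV are understated and NPV is overstated; sensitivity also shifts if clearance depends on the test result. The accuracy sentence contains nothing that prevents this comparison.

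The direction is firm for any informative test. The size is not known. The illustrated fall in specificity of about 14 to 19 percentage points (85.0 − 71.0 and 85.0 − 65.7) rests entirely on assumed prevalence, sensitivity, specificity and clearance, on a fully treated group and on no recovery of fibrotic nodes. It would be smaller in a pooled cohort and much smaller if fibrotic nodes are counted as previously positive.

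This should be fixed before analysis. It is not a defect that puts the study's main result at risk: the endpoint is descriptive and secondary, and the primary endpoint is untouched.

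**What to change.** Under Secondary study parameter(s), extend the accuracy sentence to state the following:

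1. Accuracy of staging EUS and PET-CT is reported separately by neoadjuvant status, with patients operated without neoadjuvant therapy as the main estimate.
2. In treated patients, restaging (PET-)CT is evaluated against post-treatment pathology and reported on its own, showing whether the scan included PET.
3. In treated patients, staging EUS and PET-CT are compared with nodes that are either viable-positive or fibrotic, as the pretreatment reference.

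Under Pathology, say whether fibrotic nodes without vital tumor cells count as metastatic or are only recorded, so that the third item has a fixed definition.

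The cost is a change of analysis wording. Fibrotic nodes are already recorded and restaging scans are generally made. The price is fewer patients in the main accuracy estimate and possibly a different disease spectrum, since patients operated directly may not resemble those given neoadjuvant therapy. That is a reason to show both strata. Fibrosis may also fail to mark every cleared node, so the treated estimate under item 3 should be presented as partly corrected.

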### Sample size

The aim is to include 5000 patients. This number suffices for descriptive purposes and clustering of metastases diffusion profiles into meaningful subgroups within predefined strata (patients with adenocarcinoma or squamous cell carcinoma, with and without neoadjuvant therapy, different tumor heights and invasion depths, and following a 2- or 3-field lymphadenectomy). In 2012, the incidence of esophageal cancer was 456.000 new cases worldwide [25]. Only a small percentage of patients with esophageal cancer present with curable disease at time of diagnosis. The aim is to include all 5000 patients with resectable disease in the 50 participating centers in a 2-year time period.

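### The count of metastases during follow-up is cut short by death, so it understates spread in nodal clusters with poor survival and may reverse their ranking

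*Protocol article*

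**What the plan says.** In the Protocol article, under Secondary study parameter(s), exploratory clusters of patients are formed from patterns of nodal metastases within histology and neoadjuvant-treatment groups. The clusters are then compared in three ways: descriptively on where later metastases appear; on "the number of future metastases during follow-up (Poisson regression or generalized estimation equation, whichever appropriate"); and "for 3- and 5-year overall and disease-free survival (Kaplan-Meier survival analysis"), with Cox regression to follow.

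The Follow-up section sets the window: "Patients will be followed up until 5 years after the operation". It adds that "Investigations are performed according to national guidelines".

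The Background section reports that survival after resection is known to "vary from a median of 25 to 74 months" and names nodal status as an important determinant of survival.

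The article does not state the unit counted, whether time at risk enters the model, or how death enters the comparison of counts.

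**The concern.** A total over follow-up can accumulate only while the patient is alive. The clusters are defined by nodal pattern, which the Background section ties to survival, so time under observation should be expected to differ between the groups compared. A cluster whose patients die early has less time in which metastases can be found.

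Death is also not independent of the outcome. Many deaths will follow recurrence, and a patient who dies soon after relapse contributes few further metastases because the disease was aggressive. Poisson regression and generalized estimating equations do not, as such, treat death as a terminal event linked to the count, so choosing between them does not address this.

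At stake is the ordering of nodal patterns by later spread. The Discussion section expects the results to inform radiation fields and the extent of lymphadenectomy, so a blunted or reversed ordering would matter to users.

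**Working it through.** The plan gives no expected count, rate or power for this outcome, so there is no figure to reproduce. The check sizes the distortion.

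**Inputs from the article.** Window of 60 months (Follow-up); median survival of 25 to 74 months (Background).

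**Assumptions.** Exponential survival; death is the only reason observation stops early; constant metastasis rate while alive; no offset; the chosen medians stand for two clusters.

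**Step 1: time at risk.** With L = ln 2 / median, mean time observed within 60 months is (1 − exp(−60L)) / L.

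- Median 25: L = 0.02773, exp(−60L) = 0.189, mean = 0.811 / 0.02773 = 29.2 months (19% alive at 5 years).
- Median 74: L = 0.00937, exp(−60L) = 0.570, mean = 0.430 / 0.00937 = 45.9 months (57% alive at 5 years).

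**Step 2: count ratio.** Without an offset, observed count ratio = true rate ratio × ratio of mean times. The break-even true rate ratio is the inverse of the time ratio.

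| Medians (months) | Mean time observed (months) | Count ratio at equal rates | Break-even true rate ratio |
|---|---|---|---|
| 25 v 74 | 29.2 v 45.9 | 0.64 | 1.57 |
| 25 v 50 | 29.2 v 40.7 | 0.72 | 1.39 |
| 40 v 74 | 37.3 v 45.9 | 0.81 | 1.23 |
| 25 v 30 | 29.2 v 32.5 | 0.90 | 1.11 |

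For 25 v 74 months, a true ratio of 1.5 appears as 1.5 × 0.637 = 0.96, 2.0 as 1.27 and 3.0 as 1.91.

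**Step 3: does an offset repair it?** If death is unrelated to spread, yes: dividing by time at risk returns the true ratio (1.00 instead of 0.64). To see what happens when death follows recurrence, 400,000 patients per cluster were simulated, with recurrence, then further metastases until death or 60 months. All hazards are assumed, per month.

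- *Faster death after recurrence.* Both clusters: recurrence 0.012, background death 0.003, one metastasis at recurrence, then 0.1. Additional death hazard after recurrence: 0.2 v 0.05. Raw count ratio 0.60; person-time ratio still 0.67, although spread is the same. The proportion with recurrence is 0.475 v 0.476.
- *Higher background death.* Background death 0.02 v 0.003, additional death hazard after recurrence 0.05 in both, all else equal. Raw count ratio 0.62; person-time ratio 0.94. The proportion with recurrence is 0.32 v 0.475, although the recurrence hazard is identical.
- *More spread in the poor cluster.* With recurrence 3 times higher and the same death hazard after it (0.08), the raw count ratio is 1.82. With recurrence and later metastasis rate both doubled and death after recurrence 4 times faster, it is 1.20. The poor cluster still ranks higher.

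The first case shows that an offset is not enough. The second shows that cumulative incidence alone also falls when competing deaths rise, so a cause-specific hazard is needed beside it.

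**The case against.** The strongest reply is that silence is not specification. Both named models can take a log follow-up-time offset, and the article leaves the choice between them open. A condensed article may leave the offset, the counting unit and the rules after recurrence to documents not shown. That stands: a reader might infer that the plan uses no offset, or that it counts individual lesions, but the article says neither. The point therefore rests on the outcome and models that are named, and on death after recurrence, which an offset does not fully correct.

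A second reply concerns size. The 25 to 74 months describe how survival varies across cited reports, not a contrast between clusters within one histology and treatment group. That also stands. The ratio of 0.64 is an extreme case, and the range down to a mild 0.90 belongs beside it.

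Third, the same clusters are compared on overall and disease-free survival, so early deaths would be visible next to the count. This helps the reader but does not repair the measure. Disease-free survival as usually defined combines death with recurrence and does not show where disease spread, and the article names no competing-event analysis.

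Finally, total burden and first recurrence are different questions. That is true, and it is why the count can be kept as supportive.

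**Conclusion.** The point holds as a worthwhile, inexpensive improvement to a secondary, exploratory analysis. Death cuts the count short unequally, so spread in clusters with poor survival is understated. Under the stated assumptions and without an offset, the count ratio at equal rates is 0.64 for the widest contrast and 0.72 to 0.90 for narrower ones. With an offset the bias disappears only if death is unrelated to spread; in one simulated case with equal spread, 0.67 remained.

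A reader might go further and infer that clusters with poor survival will necessarily look as if they spread less. The documents do not support that. For 25 v 74 months the ranking reverses only for true rate ratios between 1 and about 1.57; above that, the poor cluster still shows the higher count, though attenuated. Nor is the 36% shortfall (1 − 0.64) an estimate for this study. The primary endpoint is unaffected, as is the target of 5000, which the article justifies on descriptive and clustering grounds.

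**What to change.** Make time from surgery to first recurrence the main comparison of clusters on later spread. Report cause-specific hazard ratios together with cumulative incidence by site (locoregional nodal, distant nodal, organ) at 3 and 5 years, treating death without recurrence as a competing event. Keep the count as supportive only, with its unit defined (for example distinct anatomical sites at first recurrence) and a person-time offset.

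The cost is wording in the analysis plan. Date and site of first recurrence are already needed for disease-free survival, the recurrence pattern and in-field or out-field nodal recurrence, all listed under Secondary endpoints. There is a small downside: recurrences after the first no longer contribute to the main comparison. The change does not remove differences in detection between countries, since investigations follow national practice, but the main measure no longer depends on how long imaging continues after relapse.
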